### Settings

COFI is coordinated by the Unit for Social and Community Psychiatry, Queen Mary University of London (QMUL). QMUL is responsible for data collection in 11 provider organisations, that is, National Health Service (NHS) Trusts, in the UK as well as for overall project management.

Collaborating academic centres which are responsible for data collection in the remaining four countries are: (1) University of Louvain (Belgium); (2) Technische Universität Dresden (Germany); (3) University of Verona (Italy); (4) Institute of Psychiatry and Neurology of Warsaw (Poland). In each country, at least four hospitals in which a ‘specialisation approach’ is used and four hospitals in which a ‘personal continuity approach’ is used will be included in data collection. In Belgium, Germany and Poland, patients treated under ‘specialisation’ and ‘personal continuity’ of care approaches can be admitted to the same hospital as organisation of care is based on insurance arrangements or clinical decisions for the individual patients.

The hospitals in which patients are recruited are spread throughout the participating countries (see figure 2).

**Figure 2 BMJOPEN2015008996F2:**
[figure not shown]
Hospitals included in the study.

.

### Participants

#### Inclusion criteria

(1) 18 years of age or older; (2) clinical diagnosis of psychotic disorder (F20–29), affective disorder (F30–39) or anxiety/somatisation disorder (F40–49) (International Classification of Diseases—ICD—10);^27^ (3) being hospitalised in a general adult psychiatric inpatient unit; (4) sufficient command of the language of the host country to provide written informed consent and understand the questions in the research interviews; (5) capacity to provide informed consent.

#### Exclusion criteria

(1) Diagnosis of organic brain disorders; (2) too severe cognitive impairment for providing information on the study instruments.

### Baseline measures

At baseline, we will collect data on:
Sociodemographic characteristics: year of birth, gender, marital status, highest completed education level, country of birth;Social situation: employment, accommodation, living situation, friendships, self-reported benefits receipt due to low income;Psychiatric and non-psychiatric diagnoses according to the International Classification of Disease 10 (ICD-10);^27^ the primary clinical diagnosis is established from medical records or clinician’s report at discharge from hospital;Severity of illness, rated by treating psychiatrists by the Clinical Global Impression Scale (CGI);^28^Whether the current admission is the first one or not;Formal status at admission (involuntary/voluntary);Patient appraisal of inpatient care, as measured by the Client Assessment of Treatment (CAT).^29^

### Follow-up measures

In the one-year follow-up, we will compare ‘specialisation’ and ‘personal continuity’ of care approaches with reference to:

#### Primary outcome

Readmission to hospital.

#### Other clinical and social outcomes

*Clinical outcomes* including: (1) number of readmissions; (2) number of compulsory readmissions; (3) inpatient bed days, using an ad hoc schedule based on the Client Service Receipt Inventory.^30^*Social outcomes,* based on the SIX index,^31^ which captures*:* (1) employment (none; voluntary or protected or sheltered work; regular employment); (2) accommodation (homeless or 24 h supervised; sheltered or supported accommodation; independent accommodation); (3) living situation (living alone; living with a partner or family); (4) contacts with friends (not having met a friend within the past week; having met at least one friend in the past week).*Subjective quality of life*, measured by the Manchester Short Assessment of quality of life MANSA.^32^*Untoward incidents related to mental healthcare*, including: (a) deaths; (b) completed suicides; (c) serious assaults committed by patients; (d) physical violence experienced by patients; (e) suicide attempts; (f) serious side effects from pharmacological treatment requiring hospitalisation, as extracted from clinical records or obtained through phone interviews.*Social contacts,* measured as: (a) the total number of social contacts within the week preceding the assessment as reported by patients using an ad hoc instrument, adapted from the Social Network Schedule,^33^ and (b) whether or not they declare to have at least one close friend, using the specific item on the MANSA.^32^*Experienced discrimination,* measured as*:* (a) patient-reported episodes of discrimination because of mental illness, and (b) patient-reported avoidance of activities because of fear of discrimination, measured by ad hoc items.*Perceived socioeconomic status,* that is, patient self-rated standing in his/her own self-defined community and country, measured by the MacArthur Scale of Subjective Social Status.^34^
^35^

#### Costs

Service use will be measured using an adapted version of the Client Service Receipt Inventory.^30^ This will include details of:
In-patient bed days;Contacts with outpatient services;Contacts with day centres;Contacts with other community services.

We will then calculate unit costs for each service and for the different countries in order to translate service use data into costs of care.

#### Experience of care

*Satisfaction with care*, measured by the 32-item version of the Verona Service Satisfaction Scale (VSSS-32)*.*^36^*Experienced continuity of care*, explored by a set of questions designed during the study preparation phase. The questions explore: a) whether patients, following discharge, have met any of the psychiatrists or other mental health professionals that they saw in hospital; b) if yes how many psychiatrists or mental health professionals and what type of professionals; c) how long was it in weeks between hospital discharge and first outpatient contact; and d) whether they feel this duration was too long, too short or just right.Qualitative semistructured interviews will explore the in-depth experience of providing care (clinicians) and receiving care (patients) within specialisation or continuity of care approaches. Topic guides are being developed to constitute a discussion guide for the interviews. These are based on the same set of themes and topics for patients and clinicians:
*Transition between hospital and outpatient services*: admission to hospital; discharge and transition between hospital and outpatient treatment; transition between different outpatient settings.*Continuity of care*: management/coordination of treatment; staff behaviour and skills; sharing of information between different professionals; provision of information to patients.*Patients’ and carers’ involvement*: patients’ and carers’ involvement in treatment planning; how patients’ and carers’ preferences are reflected in the choice of specific settings, services and treatment options.*Accessibility and availability*: appropriateness and timeliness of care provided; cooperation of mental health services with other healthcare services and with social services.

### Procedures

#### Establishing exposure to ‘specialisation’ or ‘continuity’ of care approach

To reflect differences in how mental healthcare services operate in the five countries, different procedures are used to ascertain exposure status to either a ‘specialisation’ or ‘personal continuity’ of care approach.

In the UK and in Italy, all patients admitted to the same hospital are treated under the same care approach, either a ‘specialisation’ or ‘personal continuity’ approach. In these countries, the local providers of care, that is, an ‘NHS Trust’ in UK and a ‘Dipartimento di salute mentale’ in Italy, may follow either the ‘specialisation’ or ‘personal continuity’ of care approach. The care is organised in the same way for all patients treated by the same provider of care which operates in a specific geographic area.

In Belgium, Germany and Poland, patients admitted to the same hospital can be treated under either a ‘specialisation’ or a ‘personal continuity’ of care approach. This is determined by patients’ health insurance arrangements (Germany) and/or by a mental health team decision in which the patient may or may not be involved (Belgium, Poland and Germany). Therefore, a patient is included in either group based on the primary hospital clinician report at discharge in Belgium, Poland and Germany.

#### Recruitment, obtaining informed consent and baseline interviews

Patients consecutively admitted to participating hospitals in each country from 1 October 2014 to 31 December 2015 are screened within two days of admission and recruited in the study. Patients will be followed-up for 1 year following their entry into the study. The end of follow-up is planned by 31 December 2016.

An internal pilot of study procedures was conducted from July 2014 to September 2014 and showed that study procedures are feasible.

First contact between the patient and the research staff takes place within two working days from the hospital admission to minimise potential selection bias due to early discharge of some patients, and to standardise the period of patient experience in the hospital. However, to ensure that as many eligible patients as possible are recruited and to increase the representativeness of the sample, there is some flexibility in recruitment. The initial contact can be postponed until the discharge if the patient wishes, or he/she is deemed to be too unwell by the clinician in charge. Before the patient is contacted by the researcher, a clinician will ask the patient for his/her assent to participate in research. If assent is obtained, the clinician introduces the researcher to the patient. The researchers explain the study and obtain written informed consent for participation in the study from the patients in face-to-face meetings. Any reason for which the interview is not conducted within two working days from the admission will be documented.

To enable an accurate estimation of selection bias, any pause in the recruitment (eg, for holidays or if all the researchers are on leave at the same time or for any other organisational reason) will be documented by specifying each day of recruitment and non-recruitment.

The overall COFI recruitment and data collection plan is reported in figure 3.

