### Analysis of clinical and social outcomes

Mixed effects models with an unstructured variance matrix will be used to assess differences in the primary outcome (rehospitalisation), and in the other clinical and social outcomes between the two groups. We will explore random effects for the hospitals or ‘specialisation’ and ‘personal continuity’ of care clusters within the hospital (in Germany, Belgium and Poland), and use fixed effects for the following covariates:
Age, gender, diagnostic group, whether or not a patient has been previously admitted, severity of illness at baseline, social situation (SIX score) and formal status of the patient at baseline.

We will check the selection bias by comparing data of our sample with the aggregate data for the total group of admitted patients during the same period.

Potential mediators of effectiveness may be: (1) the intensity of treatment, that is, sum of inpatient days and outpatient visits; (2) the experience of hospital care within the index admission, which has been shown to be predictive of better outcomes following discharge.^38^
^39^ A higher intensity of treatment or a better experience of hospital care may occur in either the ‘specialisation’ or the ‘personal continuity’ of care approach and be responsible for better outcomes.^21^
^38^ We will develop a mediation model^40^ in order to identify and explicate a potential effect of intensity of treatment and/or experience of hospital care during the index admission for assessing the effectiveness of the two approaches.^41^

Exploratory analyses to compare clinical outcomes, social outcomes and untoward events between the ‘specialisation’ and ‘personal continuity’ of care approaches will also be carried out on subgroups of patients defined by:
Age (younger or older than 40 years);Gender (males or females);Primary psychiatric diagnosis (F20–29 or F30–39 or F40–49);First or repeated admission;Socioeconomic situation (receiving state benefits due to low income or not);Migrant status (ie, country of residence different from country of birth or not);Presence of physical comorbidity/comorbidities for substance use, diabetes, cardiovascular diseases or not.

All subgroup analyses will be performed by including the relevant variables as interaction terms in the models.

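### Postponing first contact up to discharge defeats the aim of standardising hospital experience, so a CAT taken then mixes length of stay and recovery with quality of care in the mediation analysis

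*Protocol article*

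**What the plan says.** All places are in the protocol article.

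- **Recruitment, obtaining informed consent and baseline interviews.** The rule is "First contact between the patient and the research staff takes place within two working days from the hospital admission". One of its two stated purposes is "to standardise the period of patient experience in the hospital"; the other is to limit selection bias from early discharge. The same paragraph then permits delay: "The initial contact can be postponed until the discharge if the patient wishes, or he/she is deemed to be too unwell". The responsible clinician makes the second judgement. On handling the delay it says: "Any reason for which the interview is not conducted within two working days from the admission will be documented".
- **Baseline measures.** The CAT is the patient's own appraisal of inpatient care. Severity is a clinician rating: "Severity of illness, rated by treating psychiatrists by the Clinical Global Impression Scale (CGI"). No rating day or reference period is given for either.
- **Analysis of clinical and social outcomes.** Baseline severity is a fixed-effect covariate in the models for rehospitalisation and the other outcomes. One of two candidate mediators is "the experience of hospital care within the index admission, which has been shown to be predictive of better outcomes following discharge". The CAT is the only listed baseline measure that fits that description.

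**The concern.** The two-working-day window is there to make the period being appraised comparable between patients. The postponement clause removes that comparability for an unstated share of them, and one of its two triggers is being too unwell.

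A patient seen on day 2 judges two days of care, usually while acutely ill. A patient seen near discharge judges most or all of a stay, probably in a better state. A difference in CAT score between these two patients reflects length of exposure, recovery and quality of care together. The mediation analysis would read it as experience of care.

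At stake is the explanation of any difference between specialisation and personal continuity, because the plan proposes experience of care as a possible route to better outcomes. The primary comparison does not use the CAT.

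**Working it through.** **1. The rule against its aim.** The aim is the same period of hospital experience for everyone. The rule puts contact anywhere from about day 2 to discharge. With a stay of L days (not given in the article), the period appraised runs from about 2 days to L days, a ratio of up to L/2. The aim holds only for patients seen inside the window.

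**2. Is the CAT taken at that contact?** The article does not say so outright. But standardising the period of patient experience is a reason to fix the contact only if that experience is assessed then. I treat it as a condition of the point.

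**3. What this does to mediation.** Write the indirect effect as a × b, where a is the effect of care approach on CAT and b is the effect of CAT on outcome.

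- Path a: if late assessment shifts the CAT by d, and the postponed share differs between approaches by Δ, the false difference in mean CAT is Δ × d. No Δ is reported. For an assumed Δ of 5 to 20 percentage points it is 0.05d to 0.20d.
- Path b: even with Δ = 0, late patients differ in illness state, which may itself predict readmission. Part of the CAT–readmission association can then come from timing and illness.

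Neither d nor the share postponed is in the article, so this cannot be turned into a figure.

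**4. The benchmark for the primary outcome.** The plan targets 27.5% versus 32.5%, with 80% power at 5% (taken as two-sided, 1:1). The standard two-proportion formula gives 1,318 per group, and 1,358 with continuity correction. 2 × 1,358 = 2,716, the plan's own figure before clustering. The yardstick is therefore 5 percentage points. Nothing here changes that sample size.

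**5. Severity adjustment, if the CGI were rated late on current state.** Simple arithmetic: false difference in mean CGI = difference in postponed share × CGI fall over the stay. On assumed inputs:

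- 0.05 × 1 = 0.05 points
- 0.10 × 1.5 = 0.15 points
- 0.20 × 2 = 0.40 points

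To carry late rating through to readmission, an illustrative simulation used 2,000,000 patients and a linear model adjusting for severity. Its assumptions, none from the article, were:

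- the sickest 10%, 20% or 30% are rated late;
- their severity is understated by 0.5, 1.0 or 1.5 SD;
- readmission rises 5 points per SD of severity;
- the log-odds of exposure are 0.1 or 0.3 per SD of severity.

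Added bias = estimate adjusting for measured severity − estimate adjusting for true severity, in percentage points:

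| Late share | Understatement | Log-odds per SD | Unadjusted | True severity | Measured severity | Added bias |
|---|---|---|---|---|---|---|
| 10% | 0.5 SD | 0.1 | 0.54 | 0.04 | 0.05 | 0.01 |
| 20% | 1.0 SD | 0.3 | 1.34 | −0.11 | 0.10 | 0.21 |
| 30% | 1.5 SD | 0.3 | 1.47 | −0.01 | 0.69 | 0.70 |

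The first and last rows are the ends of the range over all 18 settings. The largest added bias is 0.70/5 = 14% of the target difference. Even there, adjusting for the mismeasured severity moves the estimate from 1.47 to 0.69, so it still removes about half of the confounding. Adding a late-assessment indicator brought the estimate back to the true-severity result in every setting, as expected when the shift is constant.

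**The case against.** The flexibility is deliberate and well justified. The article wants as many eligible patients as possible, requires capacity to consent, and acknowledges under Potential challenges that many patients cannot consent in the first days. A strict window would probably lose very unwell patients and cause a worse selection problem. That stands, and the fix leaves the clause alone.

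Timing covariates and rating instructions normally sit in the analysis plan, the full protocol or the case report form, and the data collection figure is not shown. That also stands: a missing CGI rating day, or a missing timing covariate taken alone, is no finding. What remains is a stated rule that undoes its own stated purpose.

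A reader might infer more than the article supports:

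- **That severity is understated in the sickest patients.** What may be postponed is contact with research staff. The CGI is rated by the treating psychiatrist, and nothing ties it to that contact. Delay may also be at the patient's wish, so late patients are not all among the sickest, and discharge is an outer limit, not the usual time.
- **That postponement differs between approaches.** A clinician decides under both. Clinicians working under continuity may know their patients better, so a difference is possible, but the article reports none.
- **That adjustment would add bias overall.** The illustration points the other way, and diagnosis, previous admission, formal status and SIX score are also in the model.
- **That baseline CGI carries the hypothesis about severe illness.** That hypothesis is framed by disabling diagnoses, comorbidity and social need. The CGI is not a subgroup variable.

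**Conclusion.** The point holds for the CAT, on the condition that it is completed at first contact. The period appraised then runs from about two days to a whole stay, the delay is partly tied to illness state, and the mediation result for experience of hospital care cannot separate quality of care from length of exposure and recovery. Documenting the reason for a delay does not correct this. The size is unknown, because neither the share postponed nor the length of stay is given.

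For the primary outcome the concern is conditional and probably small: about 0.01 to 0.7 percentage points against 5, and only if the CGI is rated at the postponed contact on current state. That range rests wholly on assumed inputs and a simplified model without clustering. The matter is worth correcting, but it does not threaten the main comparison.

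**What to change.** - Keep the postponement clause.
- Derive days from admission to baseline assessment for every patient. The article does not list this variable, but deciding which interviews fall outside the window already requires both dates.
- Include that variable, or a late-assessment indicator, in the CAT mediation model.
- Repeat the mediation analysis and the severity-adjusted primary analysis in patients assessed within two working days.
- State that the CGI refers to the state at admission in all patients, whenever the interview takes place.

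**Cost.** One derived variable, one sensitivity analysis and one line of rating instruction. The within-window subset is smaller and less representative. Time to assessment arises after exposure and may itself depend on the care approach, so the adjusted and restricted mediation results should be read together. CGI ratings made retrospectively are somewhat less reliable, and using them only for late patients creates a second mode of rating linked to illness. At the reported status 4,484 patients had already consented (4,484/6,000 = 75% of target), so a new CGI instruction would reach only later recruits prospectively. The timing variable should be available for everyone if those dates were kept.

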**Figure 3 BMJOPEN2015008996F3:**
[figure not shown]
COFI recruitment and data collection plan. COFI, Comparing policy, framework, structure, effectiveness and cost-effectiveness of functional and integrated systems of mental healthcare.

#### Data collection at one-year follow-up

Clinical outcomes, employment, accommodation, living status, friendships, untoward events and indicators of care costs will be followed up for the *entire sample* via *medical records or telephone contact*.

To assess patients’ subjective quality of life, global social contacts, experienced and anticipated discrimination, perceived socioeconomic status, satisfaction with care, contacts with primary and secondary care professionals, and for patients’ experienced continuity of care we will randomly select a *subsample of patients, who will be interviewed face-to-face*.

Patients and clinicians interviewed for the *qualitative study* will be purposively selected from among those included in the entire sample. Selection criteria are reported in the following paragraph.

### Sample size determination

The sample size for the quantitative study was calculated with the aim to detect a 5% difference in rates of re-admissions (ie proportion of patients re-hospitalised during the one year follow up) between the two care approaches from 27.5% to 32.5% with 80% power at the 5% significance level.

The sample size required for an individual-level comparison not considering clustering of outcomes within centres and hospital would be 2716 patients.

We calculated an average cluster size per hospital of 150 patients recruited over one year. Taking into account a 15% drop out rate, the average number per hospital of patients recruited and followed up will be 128. The variance inflation factor (or design effect, IF) is given by IF=1+(m−1)×ρ; where m=cluster size, and ρ=ICC (inter-cluster correlation coefficient). The ICC in a cluster with such a large number of patients is expected to be very small.^37^ With m=128 and ρ=0.007, IF is 1.90, and the adjusted sample size is N=5162 (1034 per country), requiring eight hospitals per country with an average number of 150 patients recruited per hospital, ie 1200 patients per country and 6000 overall.

We will carry out follow-up face-to-face interviews with a subsample of patients who will be 18–65 years of age. The patients will be stratified based on diagnostic group (ICD codes: F20–29, F30–39, F40–49)^27^ and on whether the index admission was their first one or they have had previous hospital admissions. We will aim to interview 30 patients per stratum, resulting in 360 patients per country (60×6 clusters) and an overall sample of 1800 patients (360×5 countries).

For the in-depth interviews, we will purposively select 40 patients and 13 clinicians in each country, resulting in a total sample of 200 patients and 65 clinicians.

Within the sample, there will be a mix of: (1) patients treated with ‘specialisation’ and ‘personal continuity’ of care approaches; (2) those who were rehospitalised during the follow-up and those who were not; and (3) patients with different diagnoses (F20–29, F30–39, F40–49).

Clinicians will be included taking into account: (1) the care approach (‘specialisation’ or ‘personal continuity’) adopted by the service they work within and (2) their qualification: psychiatrists, psychologists, nurses/social workers.

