## Design and methods

### Study design

COFI is a natural experiment, prospectively following up for 1 year patients who, at the point of entry in the study, are hospitalised within care services adopting either a ‘specialisation’ or ‘personal continuity’ approach. Participating sites are located in five countries (Belgium, Germany, Italy, Poland and UK). In these countries both approaches are present, although practice, traditions, policies and funding of mental healthcare vary significantly.

Each included patient can only be treated within either a ‘specialisation’ or ‘personal continuity’ care approach, and the exposure of patients to either approach is outside of the control of investigators and hence, naturalistic. Allocation to either model is based on the given organisation of care in a defined geographical area (UK, Italy), on a clinical decision and patients’ choice (Belgium, Poland), or on insurance arrangements (Germany).

The methodology of a natural experiment has the main advantage of allowing comparisons of the two approaches without altering already established routine provision of care.

However, this implies that no randomised allocation of patients to different approaches is possible. Given the risk of bias associated with a non-randomised design, adjustment for potential confounders is of paramount importance.^26^ In our study, potential confounders will be adjusted for by exploring random effects at a hospital level which will provide an estimate of the potential variability of practice and outcomes both within countries and in different services within the countries.

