### Potential challenges

Patients will be recruited during the first days of hospital admission. Many patients may not be able to give consent or, even if they are, be unwilling to participate in the study because they are severely distressed. A number of patients admitted during the weekend and discharged after a few days may be difficult to contact. In order to enable researchers to promptly screen all admitted patients, we have established close links with the hospital staff. Presentations/refreshers on the study at all sites are carried out to make sure that all the clinical staff in the hospitals are informed on the study and information on new admissions is quickly passed on to the researchers.

One important challenge for the follow-up relates to the different ways in which medical records are stored in different countries. In UK and Italy, continuous electronic medical records, including information on a given patient within and outside the hospital, are available; however, this is not the case in other countries. Therefore, patients will receive short phone interviews at follow-up in Germany, Belgium and Poland. This may determine attrition rates higher than 15% for the primary outcome in these countries; in UK and in Italy, attrition rates are likely to be lower than 15%. The potential imbalance in missing data at follow-up among countries will be controlled in the mixed model adjusting for fixed effect of baseline patient-level variables and random effects at a hospital level.

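### The 6000 recruits stated as required leave 5100 analysed patients after the article's own 15% drop-out, slightly fewer than its stated 5162

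*Protocol article*

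**What the plan says.** All the figures are in the *Sample size determination* section of the protocol article. The target is a difference in one-year readmission "between the two care approaches from 27.5% to 32.5% with 80% power at the 5% significance level". Without clustering the section needs 2716 patients: "not considering clustering of outcomes within centres and hospital would be 2716 patients". It starts from 150 recruits per hospital and allows for loss: "Taking into account a 15% drop out rate, the average number per hospital of patients recruited and followed up will be 128". With 128 as the cluster size and an intracluster correlation of 0.007, it states "IF is 1.90, and the adjusted sample size is N=5162 (1034 per country". It then turns this into recruitment, "requiring eight hospitals per country with an average number of 150 patients recruited per hospital, ie 1200 patients per country and 6000 overall".

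Three other places bear on the point. The abstract gives 6000 as a minimum, and *Settings* gives the hospitals per approach as minima. *Study design* says that "the exposure of patients to either approach is outside of the control of investigators". On loss to follow-up in Germany, Belgium and Poland, *Potential challenges* says "This may determine attrition rates higher than 15% for the primary outcome in these countries", and it expects loss below 15% in the UK and Italy.

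**The concern.** The design effect is computed on the followed-up cluster size, so the 5162 it produces is the number needed in the analysis. The recruitment presented as meeting that need should therefore leave at least 5162 after 15% loss, and it does not. Readers will rely on the stated sample and 80% power when they interpret a null result, and the *Discussion* claims power to detect small differences, with 5% in rehospitalisation as its example. The figures in the chain should agree with each other. The 2716 at its base also carries an assumption about group sizes that the text does not state.

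**Working it through.** **Inputs (all from *Sample size determination*).** Rates 27.5% and 32.5%; power 80%; significance level 5%, taken as two-sided because that reproduces the stated figure; 150 recruits per hospital; 15% loss; m = 128; ICC = 0.007; 8 hospitals in each of 5 countries, so 40 hospitals.

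**1. The unclustered figure reproduces.**
- Pooled-variance formula with d = 0.05 and mean rate 0.30: n = [1.960·√(2·0.30·0.70) + 0.842·√(0.275·0.725 + 0.325·0.675)]² / 0.05² = (1.2702 + 0.5446)² / 0.0025 ≈ 1317.4.
- Continuity correction: n′ = (n/4)·[1 + √(1 + 4/(n·d))]² ≈ 1357.1, rounded up to 1358 per group.
- Total 2 × 1358 = **2716**, as stated. This figure is for two equal groups.

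**2. The cluster-adjusted figures reproduce.**
- IF = 1 + (128 − 1) × 0.007 = 1.889, which the article carries as 1.90.
- 1358 × 1.90 = 2580.2, rounded up to 2581 per group; 2 × 2581 = **5162**.
- 5162 / 5 = 1032.4, rounded up to an even number: **1034** per country.

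So 1.90, 5162 and 1034 are upward rounding and not errors.

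**3. The step to recruitment does not close.**
- 5162 / 128 = 40.3 hospitals, but 40 are used. The gap arises here.
- 6000 × 0.85 = **5100**, which is 62 short (62/5162 = 1.2%). With the rounded 128, 40 × 128 = 5120, which is 42 short (0.8%).
- Per country: 1200 × 0.85 = 1020, or 8 × 128 = 1024, against 1034.
- With the unrounded IF the need is 2716 × 1.889 = 5130.5, so 5131. Both 5100 and 5120 still fall below it.

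**4. Recruitment that would match.**
- 5162 / 0.85 = 6072.9, so **6073** (about 152 per hospital).
- 5131 / 0.85 = 6036.5, so **6037**, holding m at 128. If the extra recruits come from the same 40 hospitals, m rises slightly. Solving N = 2716 × [1 + (N/40 − 1) × 0.007] gives N = 2696.99 / 0.5247 ≈ 5140, or 6048 recruits, still below 6073.

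**5. Power at 5100, equal groups.**
- Effective size per group: 5100 / 1.889 / 2 = 1349.9.
- Inverting the continuity correction: n = n′·[1 − 1/(n′·d)]² ≈ 1310.2.
- z = (√(1310.2 × 0.0025) − 1.2702) / 0.6471 ≈ 0.834, so power ≈ **79.8%**.
- With IF 1.90 the same steps give 79.5%. The matching values at 5162 are 80.3% (IF 1.889) and 80.0% (IF 1.90). The shortfall costs about half a point. Without continuity correction, power at 5100 is about 81%.

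**6. Why imbalance cannot be read off a single design effect.** *Analysis of clinical and social outcomes* allows for approach-within-hospital clusters in Germany, Belgium and Poland. Assume independent clusters with ICC 0.007, UK and Italy balanced, 127.5 analysed per hospital, and a 70:30 split in each hospital of those three countries.
- Larger group: 24 × 89.25 / 1.618 + 8 × 127.5 / 1.8855 ≈ 1324 + 541 = 1865 effective patients.
- Smaller group: 24 × 38.25 / 1.261 + 541 ≈ 728 + 541 = 1269.
- Power is about 84–85% (with and without continuity correction). An 80:20 split in those countries gives about 81–82%.

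**7. Attrition can fall either side of 15%.** With equal country targets, overall loss is (3x + 2y)/5, where x applies to the three phone-interview countries and y to the UK and Italy. The documents give neither figure. Assumed values: x = 20%, y = 10% gives 16%; x = 20%, y = 5% gives 14%.

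**The case against.** The strongest reply is that the gap is a rounding matter. It is at most 62 of 5162, power stays near 80%, and 6000 is a minimum. *Current study status* reports 4484 consents in the ninth of 15 months. Extrapolated at constant pace that is 4484/9 × 15 ≈ 7473 recruits, or about 6352 after 15% loss. If these came from 40 hospitals, m would be 158.8, IF 2.105 and the need about 5716, so the requirement would be met. This stands. It makes the point minor and may close the gap in practice, but the stated figures still do not agree.

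A second reply is that a condensed article may leave the allocation ratio and power under alternative scenarios to the full protocol. That also stands, and the absence of a power table is not held against the article. The remark about equal groups is narrower: the printed 2716 contains that assumption, and a short clause would make it visible.

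A reader might go further and infer that the study is clearly underpowered, because allocation is naturalistic and three countries may lose more than 15%. The documents do not support this. They give no split. *Settings* plans at least four hospitals of each approach in every country. The smaller clusters in step 6 can offset an imbalance. Overall loss above 15% is possible but not established, since the same passage expects lower loss in the UK and Italy.

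**Conclusion.** This is a minor arithmetic inconsistency. The requirement of 5162 analysed patients (1034 per country) is not delivered by 6000 recruits less 15%, which is 5100 (1020 per country), or 5120 (1024 per country) with the rounded cluster size. The shortfall is 0.8% to 1.2%. Power at 5100 is about 79.8% by the continuity-corrected formula with IF 1.889, assuming equal groups, ICC 0.007 and a uniform cluster size. The rounding to 1.90, 5162 and 1034 is sound. The base figure of 2716 holds for equal groups, which the design does not guarantee. What an unequal split would cost cannot be determined from the documents, and a material loss of power is not shown.

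**What to change.** Restate the figures in *Sample size determination* in one of two ways:

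- Keep 5162 as the number analysed and give the matching recruitment at 15% loss as 6073. With the unrounded design effect of 1.889, give 5131 analysed and 6037 recruited.
- Keep 6000 recruits and state 5100 analysed (1020 per country), with about 79.8% power by the same continuity-corrected formula.

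In either case, add a clause saying that 2716 is 2 × 1358 and assumes groups of equal size, and that naturalistic allocation does not guarantee this.

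The cost is a change of wording. No procedure changes, and at the reported pace recruitment was already heading past 6073.
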